### 1. Specific Aims

Test the independent and combined effects of common front-of-package (FOP) marketing tactics (e.g., 100% Vitamin C claims and fruit images) and added sugar warning labels and nutrition disclosures (e.g., teaspoons of added sugar per serving) on parents' perceptions and beverage choices for their children using a randomized controlled design in a unique online retail setting, and examine differences by race/ethnicity, income, and SNAP/WIC participation.

### 2. Background and Significance

#### 2.1 Provide the scientific background and rationale for the research.

Fruit drinks are the most widely consumed sugar-sweetened beverages (SSBs) by 0-5-year-olds. Parents purchase these drinks for their children in part due to misperceptions that they are healthful, which may be driven by FOP health claims and imagery. The Food and Drug Administration (FDA) is considering changes to FOP marketing regulations but lacks supporting data on how different marketing tactics influence consumer purchases and perceptions. The proposed research aims to inform federal regulation and fill knowledge gaps on the influence of FOP marketing on behavior and product perceptions, which can then be used to determine effective approaches to correct health misperceptions of fruit drinks.

#### 2.2 Describe the significance of the research, and how it will contribute to generalizable knowledge.

There are large gaps in our knowledge on how FOP marketing tactics on beverages purchased by households with young children affect parents' perceptions and selections, and the effects of changing or countering aspects of FOP marketing to reduce deception or better communicate nutrition information. The majority of prior consumer research on FOP labeling has been conducted in laboratory or online experiments with unbranded beverages; there are limited data on the impact of FOP claims and virtually no data on the impact of FOP imagery on product selection in more realistic retail settings, in which FOP claims, imagery, and branding interact to maximize the influential aspect of the label on purchase behavior. Additionally, there have been no studies to date investigating how legally feasible nutrition warnings and disclosures (e.g., teaspoons of added sugar per serving) could be used with common FOP marketing tactics to correct misperceptions or influence product selections. Preliminary evidence on FOP warning labels suggest they may be effective at reducing SSB purchases, but policy proposals mandating FOP warning labels in the U.S. have been unsuccessful. Disclosures designed to correct misleading advertising may be more legally and politically feasible and as effective, but this has not been studied. Our proposed research contributes to these important knowledge gaps by testing the effects of modifications to existing FOP marketing strategies on parents' perceptions and purchases of SSBs, using a randomized trial in an online store.

Results of this work are timely and can directly inform federal regulation of claims and imagery on food and beverage packaging. The FDA is currently considering changes to claims and other FOP labeling as a part of its Nutrition Innovation Strategy, which aims to reduce preventable death and disease related to poor nutrition, in part by empowering consumers to make better, more informed decisions. The FDA is particularly interested in exploring science-based modifications to claims related to added sugars, especially on products that contain fruit. However, the agency lacks supporting data on how different FOP claims and marketing influence consumers' beverage perceptions and purchase intentions. We have discussed our research intentions with several FDA Senior Advisors for Nutrition Policy, and they have expressed strong support and interest in our work.

### 3. Research Locations and Collaborating Sites

*Research Locations refer to the geographic location that the research will take place, not to the institutions or researchers you may be collaborating with. All Research Locations should be listed in ESTR as a [Research Location](#).*

*Collaborating Sites refer to institutions or researchers that are also taking part in the research study. All Collaborating Sites should be listed in ESTR as a [Participating Site](#).*

- 3.1. **Where will the research activities take place?** (check all that apply)  
☒ **At Harvard;** list any non-Harvard Longwood Medical Area (LMA) Schools here: [A list of all Harvard Schools can be found here.](#)  
☐ **At another location in Massachusetts;** specify here:  
☐ **In another state in the U.S.;** specify here:  
☐ **Internationally;** specify here:
- 3.2. **Describe the sites or locations where the research will be conducted or overseen by the Harvard PI.** (If conducting the study virtually or remotely, indicate the location of the researcher who is conducting the study.)  
  
Data collection will occur online via Qualtrics. Data will be analyzed by researchers at the Harvard T.H. Chan School of Public Health. Due to COVID restrictions, the researcher analyzing the data will be doing so remotely from Cambridge, MA.
- 3.3. **Describe plans for communication among sites regarding adverse events, interim results, protocol modifications, monitoring of data, etc.** ☒ N/A.
- 3.4. **Describe any local (international or state) laws, regulations, and/or customs affecting the research (e.g., age of majority, mandatory reporting requirements, etc).** ☒ N/A.
- 3.5. **Identify any approvals or permissions required of collaborating institutions, community leaders, or government officials, including approval from another IRB or local research ethics committee.** Upload copies to the "Study-Related Documents" page in ESTR. ☒ N/A.
- 3.6. **Will you collaborate with any researchers not affiliated with Harvard to carry out this study?**  
☒ **No** ☐ **Yes:** If yes, list which institutions they are affiliated with. If they are not affiliated with an institution, indicate that here. If yes, also indicate their responsibilities and scope of work in conducting this research.
- 3.7. **Will your collaborators interact with human subjects, have access to identifiable data/specimens, and/or be responsible for the design, conduct, oversight, or reporting of the research?**  
☒ **No** ☐ **Yes:** If yes, indicate if the collaborators will obtain their own IRB review.
- 3.8. **Will any institution conducting research activities as part of this study, including collaborators, rely on Harvard LMA for IRB review?**  
☒ **No** ☐ **Yes:** If yes, list each relying institutions, their site responsible Investigator, and describe what research activities will be conducted there.

**5. Study Design**

**5.1. Describe the study design type.**

Randomized Controlled Trial

**5.2. Does the study involve more than one participant group?**

☒ No ☐ Yes: *If yes, identify each group here and throughout all applicable sections.*

**5.3. Indicate the total duration of a participant's involvement.**

15-minute online purchasing task and survey

**5.4. Indicate the total number of participants to be screened (if applicable) and/or enrolled (i.e., signed consent form). If the proposed research involves secondary data analyses only, indicate the number of data, documents, records, and/or specimens that will be obtained.**

5,000 participants will be recruited to take part in our study.

**5.5. List inclusion and exclusion criteria, including age ranges of all participants, and describe the screening process. Provide a rationale for any specific exclusion criteria.**

We will recruit 5,000 primary caregivers of children 0-5 years old to participate in a randomized controlled online shopping experiment, with oversampling for Hispanic and black participants. We will use Qualtrics, a firm that recruits research participants through their online panels and other online communities, social networks, and websites, to recruit participants with the following eligibility criteria: 1) primary caregiver of a child 0-5 years old; 2)  $\geq 18$  years old; and 3) U.S. citizen. For our study, participants will be sent an invitation asking them to "take a survey" to avoid selection bias based on survey topic. Participants will also be required to answer a data integrity check question near the end of the survey (i.e., "what month is it?"). Those who answer incorrectly will be excluded from analyses.

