**5.6. Describe study procedures.**

After providing informed consent, participants will complete a 10-15 minute survey. They will be asked to answer all questions based on their oldest child 0-5 years old, and will provide the age of the child. First, participants will be told to use a mock online retail store to choose a beverage for their child that will be sent to them (or they will receive \$5). In reality, at the end of the study, we will debrief participants on the study purpose and inform them that instead of receiving the beverage they selected, all participants will be compensated with \$5 through the survey distribution company (twice the value of a typical beverage in the store). This very minor deception enables us to incentivize participants to behave as they normally would when shopping online and to minimize potential social desirability bias introduced by participating in a study. Participants will then be shown images of 12 different beverages (random order) consisting of commonly purchased beverages in various categories, with oversampling for fruit drinks (e.g., 6 fruit drinks, 1 milk, 2 100% juices, 2 regular sodas, and 1 water). The variety will provide a realistic shopping scenario for generalizability. Participants will be required

to click on beverages to see an enlarged package before choosing. After selecting their beverage, participants will advance in the survey to view four randomly ordered fruit drinks one at a time and answer questions about their health knowledge, product beliefs, and purchase intentions. See **Appendix A** for full survey (consent + debriefing language) and **Appendix B** for images.

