**Label Randomization.** Caregivers will be randomized using simple randomization via the Qualtrics platform to see fruit drinks in our online store and survey with one of the following seven label conditions (**Appendix B**). The first condition (*claim & imagery*, control) will represent the status quo and contain a 100% Vitamin C claim and fruit imagery. Conditions 2-4 will involve the removal of package elements for fruit drinks high in added sugar (“high sugar”,  $\geq 10\text{g/serving}$ , 20% DV): Condition 2 (*imagery only*) will have fruit imagery but no 100% Vitamin C claim on high-sugar fruit drinks; Condition 3 (*claim only*) will have a 100% Vitamin C claim but no fruit imagery on high-sugar fruit drinks; and Condition 4 (*no claim or imagery*) will feature no imagery or claims on high-sugar fruit drinks. Conditions 5-7 will involve the addition of package elements. Condition 5 (*imagery, claim, & text % fruit juice disclosure*) will show a text description of the percent fruit juice in each fruit drink, to see if it changes the effects of the claim and imagery. The sixth (*imagery, claim, & added sugar warning*) and seventh conditions (*imagery, claim, & added sugar warning w/teaspoons of sugar*) will test the effects of added sugar warnings.

**Primary Outcomes:** The primary outcomes will be total calories and grams of added sugar purchased in the online store task (averaged by condition). We will also examine the percentage of people in each condition that purchased a drink high in added sugars ( $>20\%$  DV) for their child, and the percentages that chose each category of drink (fruit drinks, 100% juice, etc).

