**16.2. Is there a sample size/power calculation?**

☐ No ☒ Yes: *If yes, describe the calculation and the scientific rationale, and, if applicable, by site and key characteristics such as participant demographics.*

To compare the primary outcome of total kcals purchased across the seven groups, we determined that a sample of 4,900 participants (700 per group) would provide at least 80% power to detect an 18-kcal difference between each group, assuming an alpha of 0.05. This estimate is based on effect sizes found in our previous labeling research. It is typical to exclude a small number of participants in online studies (e.g., for failing data integrity check questions), so we will recruit 5,000 participants. Qualtrics has confirmed that this will be feasible given our inclusion criteria.

**17. Costs and Compensation** ☐ N/A. *Skip to next section.*

**17.1. Identify any costs that participants may incur during the study, including transportation costs, childcare, or other out-of-pocket expenses.**

None

**17.2. Identify remuneration that participants may receive during the study. Specify the amount, timing of disbursement, and method (e.g. money, gift cards, in-kind, incentives, raffles, and transportation). Describe how compensation will be calculated and paid if a participant withdraws. If any participant will receive a single payment more than \$100, or \$600 or more in one calendar year, refer to [Harvard University Financial Policy on Human Subject Payments](#).**

Participants will receive a \$5 gift card at the end of their participation in the study, dispensed through Qualtrics via participant emails. They will receive compensation regardless of whether they stop the study early.

**18. Sharing Study Results** ☐ N/A. *Skip to next section.*

**18.1. Describe the plan to share study results with individual participants, the participant group/community, and/or others.**

Results will be published in a scientific journal, and will be shared via webinar with the FDA.

**19. Research Related Injuries** ☒ N/A. *Skip to next section.*

19.1. Describe plans for medical care and compensation for research-related injuries.

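### Excluding people who fail an integrity question asked after the labels and the primary outcome leaves the analysed comparison no longer fully protected by randomisation

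*Protocol*

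**What the plan says.** The protocol fixes the order of events in sections 5.5 and 5.6.

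- **Randomisation and exposure.** "Caregivers will be randomized using simple randomization via the Qualtrics platform to see fruit drinks in our online store and survey" under one of seven label conditions (5.6, Label Randomization). The assigned label therefore applies in both the store and the survey.
- **Store task.** It opens the survey: "First, participants will be told to use a mock online retail store to choose a beverage for their child" (5.6).
- **Primary outcomes.** "The primary outcomes will be total calories and grams of added sugar purchased in the online store task" (5.6, Primary Outcomes).
- **Further exposure.** "After selecting their beverage, participants will advance in the survey to view four randomly ordered fruit drinks one at a time and answer questions" (5.6).
- **Check and consequence.** "Participants will also be required to answer a data integrity check question near the end of the survey", and then "Those who answer incorrectly will be excluded from analyses" (5.5). The example question asks which month it is. No outcome or analysis set is exempted.

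Section 16.2 plans for these exclusions: "we determined that a sample of 4,900 participants (700 per group"), with 5,000 recruited to allow for a small number of removals. The protocol describes no analysis that retains those who fail, and gives no reason for placing the question late.

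**The concern.** Randomisation makes the seven groups comparable as they were formed. It does not do so for a subset picked later by something the participant does after seeing the randomised material. Here the selecting event is a survey answer given after two rounds of label exposure, and it discards a primary outcome already recorded.

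The conditions differ in what the package shows: conditions 2 to 4 remove elements, while 5 to 7 add a disclosure or a warning. It is possible, though not shown, that the share failing, or the kind of person failing, differs by condition. Section 16.1 limits covariate adjustment on the strength of the randomised design, so the analysis relies on the protection that this rule weakens. At stake is a shift in each pairwise difference in calories and added sugar that the data cannot reveal once failers are dropped.

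This is a rule the protocol states, not a detail it leaves to a statistical analysis plan.

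**Working it through.** **Inputs from the protocol (16.2).** 700 per group, seven groups, 5,000 recruited, an 18-kcal difference, at least 80% power, alpha 0.05 (taken as two-sided).

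**Inputs not in the protocol.** The SD of calories purchased, failure rates by arm, and the calorie difference between failers and passers. The SD is solved backwards; the others are assumed and varied.

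**Step 1: the plan's own figures.** 7 × 700 = 4,900, and 4,900 / (1 − 0.02) = 5,000, so the implied exclusion rate is 100 / 5,000 = 2.0%. The 80% power cannot be reproduced directly because no SD is given. Solving for it:

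SD = 18 / [√(2/700) × (1.960 + 0.842)] ≈ 120.2 kcal.

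The standard error of a pairwise difference is then 120.2 × √(2/700) ≈ 6.4 kcal.

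**Step 2: bias formula.** In an arm with failure rate f, let D be the mean kcal of failers minus that of passers. The mean of all randomised is the passers' mean plus f × D. Analysing passers only therefore shifts an arm difference, in absolute value, by

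|f1 × D1 − f0 × D0|.

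With equal D this reduces to |f1 − f0| × D.

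**Step 3: scenarios with equal D.** Type I error is for an unadjusted two-sided 0.05 test with 700 per arm and SD 120.2.

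| f0, f1 | D (kcal) | Bias (kcal) | Share of 18 | Type I error |
|---|---|---|---|---|
| 2%, 2% | any | 0 | 0% | 5.0% |
| 1%, 3% | 60 | 0.02 × 60 = 1.2 | 6.7% | 5.4% |
| 1%, 3% | 120 | 0.02 × 120 = 2.4 | 13.3% | 6.6% |
| 5%, 8% | 120 | 0.03 × 120 = 3.6 | 20% | 8.7% |
| 5%, 10% | 120 | 0.05 × 120 = 6.0 | 33% | 15.4% |

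The first three rows lie near the planned 2%. The last two need far more exclusions than the plan expects. D = 120 is about one full SD, a large gap.

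**Step 4: equal failure rates do not guarantee zero.** Suppose 2% fail in both arms, the label changes passers' mean by 18 kcal, and failers ignore it. Then D1 and D0 differ by 18, and the passers-only estimate differs from the all-randomised effect by 0.02 × 18 = 0.36 kcal. That is small, but it is a different quantity.

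**Step 5: effect of the fixes on power (SD 120.2).** Check before the randomiser, 2% screened out: 5,000 × 0.98 = 4,900 randomised, 700 per arm, 80.0%. Keeping all 5,000: 714 per arm, 80.8%. The second figure is an upper limit, since non-completers, withdrawals and duplicates would reduce it. The gain is in validity, not power.

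**The case against.** The strongest reply is that the problem is small and partly a matter of choice. The question has nothing to do with the label. Every arm sees the same number of products and survey items as described, so differential fatigue is conjecture. The plan expects about 2% exclusions. A 1-point difference in failure with a 60-kcal gap gives only 0.6 kcal, about a tenth of the standard error. A late check also screens the belief and intention items, and restricting to attentive respondents can be defended as an estimand.

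Most of this stands as to size. It does not justify the placement: the store choice comes first, so inattention that begins later does not bear on it, and nothing in the protocol prevents an earlier check. If attentive respondents are the target, attention can be measured before randomisation.

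Three stronger readings are tempting and not supported:

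- **That the comparison is broken or shown to be biased.** The documents show only a loss of protection.
- **That failure differs by 3 to 5 points between arms.** At 2% overall, with one arm differing from the other six, that arm would have to fail at about 4.6% to 6.3% against 1.6% to 1.3% elsewhere. A difference of that size exceeds the whole planned exclusion rate.
- **That people who stop after the store task are excluded too.** Section 5.5 removes those who answer incorrectly and sets no rule for those who never reach the question.

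**Conclusion.** The point holds as a design weakness of uncertain and probably modest size. Sections 5.5 and 5.6 together define the analysed set by an answer given after randomisation, label exposure and the recorded primary outcome, and no other section cures this.

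Near the planned 2% exclusion, the assumed scenarios give about 0 to 2.4 kcal against the 18-kcal target, with type I error up to 6.6% instead of 5%. Larger values require failures that are more common or differ more by arm. All of these rest on assumed failure rates and failer-passer differences, and the error rates also rest on an SD of about 120 kcal inferred from the power statement. The true bias could be zero. The change is worth making because the remedy is nearly free, not because harm has been demonstrated.

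**What to change.** **Preferred.** Ask the integrity question with the eligibility items, before the Qualtrics randomiser, and screen out failures there. Exclusion on this question then cannot depend on the assigned label. The cost is moving one survey item; the 4,900 target is unaffected if about 2% fail. The downside is that an early check misses inattention that begins later. That matters for the later survey items, not for the store choice.

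**If the late check is kept.** Make the primary store-outcome analysis all randomised participants who completed the survey and debriefing and did not withdraw their data, after duplicate removal, whatever their answer to the check. Use the exclusion as a sensitivity analysis and report failures by arm. The restriction to people who reached debriefing is deliberate: the opt-out in section 7.5 comes at the end of the survey, and those who stop before it were never offered it. The cost is one or two sentences.

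Neither version removes every loss after randomisation. The debriefing opt-out (7.5) and the removal of duplicate IP responses (14.1) remain, and the second version also conditions on completion. Counts by arm for each would let a reader judge them.

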**5.6. Describe study procedures.**

After providing informed consent, participants will complete a 10-15 minute survey. They will be asked to answer all questions based on their oldest child 0-5 years old, and will provide the age of the child. First, participants will be told to use a mock online retail store to choose a beverage for their child that will be sent to them (or they will receive \$5). In reality, at the end of the study, we will debrief participants on the study purpose and inform them that instead of receiving the beverage they selected, all participants will be compensated with \$5 through the survey distribution company (twice the value of a typical beverage in the store). This very minor deception enables us to incentivize participants to behave as they normally would when shopping online and to minimize potential social desirability bias introduced by participating in a study. Participants will then be shown images of 12 different beverages (random order) consisting of commonly purchased beverages in various categories, with oversampling for fruit drinks (e.g., 6 fruit drinks, 1 milk, 2 100% juices, 2 regular sodas, and 1 water). The variety will provide a realistic shopping scenario for generalizability. Participants will be required

to click on beverages to see an enlarged package before choosing. After selecting their beverage, participants will advance in the survey to view four randomly ordered fruit drinks one at a time and answer questions about their health knowledge, product beliefs, and purchase intentions. See **Appendix A** for full survey (consent + debriefing language) and **Appendix B** for images.

**Label Randomization.** Caregivers will be randomized using simple randomization via the Qualtrics platform to see fruit drinks in our online store and survey with one of the following seven label conditions (**Appendix B**). The first condition (*claim & imagery*, control) will represent the status quo and contain a 100% Vitamin C claim and fruit imagery. Conditions 2-4 will involve the removal of package elements for fruit drinks high in added sugar (“high sugar”,  $\geq 10\text{g/serving}$ , 20% DV): Condition 2 (*imagery only*) will have fruit imagery but no 100% Vitamin C claim on high-sugar fruit drinks; Condition 3 (*claim only*) will have a 100% Vitamin C claim but no fruit imagery on high-sugar fruit drinks; and Condition 4 (*no claim or imagery*) will feature no imagery or claims on high-sugar fruit drinks. Conditions 5-7 will involve the addition of package elements. Condition 5 (*imagery, claim, & text % fruit juice disclosure*) will show a text description of the percent fruit juice in each fruit drink, to see if it changes the effects of the claim and imagery. The sixth (*imagery, claim, & added sugar warning*) and seventh conditions (*imagery, claim, & added sugar warning w/teaspoons of sugar*) will test the effects of added sugar warnings.

**Primary Outcomes:** The primary outcomes will be total calories and grams of added sugar purchased in the online store task (averaged by condition). We will also examine the percentage of people in each condition that purchased a drink high in added sugars ( $>20\%$  DV) for their child, and the percentages that chose each category of drink (fruit drinks, 100% juice, etc).

